### Participants

#### Patients

We will screen all patients who previously completed a detoxification and then entered an alcohol-specific inpatient treatment program at one of three specialized addiction treatment centers in Switzerland, namely the Suedhang Hospital (Bern); the Forel Hospital (Zuerich) and the Psychiatric Hospital of Muensingen (Bern). Inclusion criteria are age 18–60 years and abstinence from alcohol for at least 4 weeks prior to the first training session. Exclusion criteria are other main psychiatric diagnoses than AUD (comorbidities are allowed as long as AUD is considered to be the main diagnosis), other severe SUD (except nicotine; Drug Use Identification Test (DUDIT [47, 48]) ≥ 25 per substance), no diagnosed neurocognitive problems (e.g., Korsakoff syndrome) in the medical history, current medical conditions preventing participation (e.g., acute infectious diseases), the inability to read and understand the participant’s information and the enrollment of an investigator, their family members, employees and other dependent persons. Written informed consent will be obtained from all patients at the beginning of the study.

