#### Alcohol-related constructs

Alcohol craving will be measured by the *Obsessive Compulsive Drinking Scale,* (OCDS-G; [61]). The items of the OCDS-G are divided into two subscales: control and consequences, and drinking obsessions.

As a second measure for craving, three specific questions will be asked [57, 58], which are scored from 0 (non-existent or never) to 10 (very strongly or always): “How strong was your urge to drink alcohol (on average) during the past 7 days?”; “Think of the moment during the past 7 days, in which the urge to consume alcohol was the highest. How strong was the urge?”; and “How often did you have the urge to drink alcohol during the past 7 days?”

Motivation to change alcohol use will be assessed with the *Stages of Change Readiness and Treatment Eagerness Scale* (SOCRATES; [62]), whereby only the subscale *Taking Steps* will be used. It indexes whether the person has already taken action to positively change their drinking behavior.

A second measure for motivation consists of three items on an 11-point Likert scale, summed up as *Motivation* [41, 63, 64]. Inspired by the framework of motivational interviewing [64], the first question “How important is it for you not to drink alcohol? What do you think about that at this very moment?” [63] will be followed by the statement “I will do everything to get my alcohol problem under control.” [64]. Third, general self-efficacy will be assessed with one question: “How confident are you that you will be completely abstinent in one year from now?” [41].

A broader concept of alcohol-specific self-efficacy will be measured with the *Alcohol Abstinence Self-Efficacy Scale* (AASE-G [65]), which assesses the patients’ expectations concerning their ability to remain abstinent from alcohol in specific high-risk situations.

Positive and negative alcohol outcome expectancies are quantified with the *Comprehensive Alcohol Expectancy Scale* (CAEQ [66, 67]). A reduced version [67] will be used to assess five dimensions of alcohol expectancies: social assertiveness and positive affect; tension reduction; cognitive impairment and physical discomfort; aggression; and sexual enhancement.

As has been done before [57, 58], *Drinking Goals* will be assessed by asking the patients whether their personal drinking goal is (1) total abstinence and hence no future alcohol use, (2) abstinence with occasional lapses, or (3) controlled and responsible drinking.

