#### Main study

Training effects on our primary outcome measures (PDA and HDD at 3-month follow-up) will be assessed with a 2 × 3 analysis of variance (ANOVA) with the factors time point (T1, T5) and training group (Alc-IT (50/50), Alc-IT (75/25) or control). Further, a Cox regression will be computed to predict the effect of the intervention on TFD (at 3-month follow-up).

Training effects on experimental test parameters will be assessed with a 2 × 2 × 3 repeated measures ANOVA with the factors measurement point (T2, T3), time of day (morning, afternoon) and training group (Alc-IT (50/50), Alc-IT (75/25) or control). Where Mauchly’s test of sphericity indicates heterogeneity of covariance, we will verify repeated measures results with Greenhouse-Geisser corrections.

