### Power calculation

The intended sample size was calculated with G*Power (Version 3.1.5, Heinrich-Heine-University Duesseldorf, Dusseldorf, Germany). In a-priori analyses (1−β = 0.8, α = 0.05), slightly reduced expected effect sizes were entered compared to earlier studies because of the additional manipulations concerning different training versions and time of training. For the 2 × 3 ANOVA to examine the training effects on the primary outcome measures PDA and HDD (with an expected effect size of f = 0.2 based on earlier studies [32]), a total sample size of *n* = 244 is needed. For the analyses of the training’s effect on TFD (the third primary outcome, estimating a small to medium effect size of w = 0.25 based on earlier studies [37], and df = 3), G*Power indicated a total sample size of *n* = 174 for the Cox regression. For the 2 × 2 × 3 repeated measures ANOVA examining training effects on experimental parameters and also taking into account the effects of time of day of the training (expecting small to medium effects of f = 0.15 and correlations of 0.4 among repeated measures based on earlier studies [107]), the necessary sample size was *n* = 180. Considering the necessary power for all analyses and similar sample sizes in all study arms (82 per intervention group), a total of 246 patients will be recruited.

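### The Cox model for time to first drink names no baseline drinking or drinking-goal term; pre-specifying one is a cheap, optional efficiency gain

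*Protocol article*

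**What the plan says.** - **Analysis.** Under Statistics, Main study, PDA and HDD are analysed with an ANOVA whose time factor is T1 and T5, so baseline drinking is part of that model. For TFD the text says only that "a Cox regression will be computed to predict the effect of the intervention on TFD (at 3-month follow-up". No covariate or stratum is listed, and none is ruled out.
- **Eligibility.** Under Patients: "Inclusion criteria are age 18–60 years and abstinence from alcohol for at least 4 weeks prior to the first training session". The article does not require patients to aim at abstinence.
- **Drinking goal.** Under Alcohol-related constructs, goal "will be assessed by asking the patients whether their personal drinking goal is (1) total abstinence and hence no future alcohol use". The other two answers are "2) abstinence with occasional lapses, or (3) controlled and responsible drinking". The readable text does not say when the question is asked, and the schedule figure could not be read here.
- **Baseline drinking.** The Timeline Follow-back (TLFB) interview at T1 covers the 90 days before detoxification and yields PDA and HDD.
- **Other adjustment.** The Trail Making Test is to be a covariate in the statistical analyses generally (Interviews and questionnaires, Other). Randomisation is stratified by gender and age group.
- **Sizing.** "In a-priori analyses (1−β = 0.8, α = 0.05" and, for TFD, "estimating a small to medium effect size of w = 0.25 based on earlier studies [37], and df = 3", giving 174 "for the Cox regression". The trial plans "similar sample sizes in all study arms (82 per intervention group), a total of 246 patients will be recruited".

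**The concern.** TFD counts any first drink after discharge. A patient who intends controlled drinking may drink early by plan, while a patient aiming at total abstinence drinks early only by lapsing. Goal, and recent drinking before admission, are therefore plausible predictors of when the first drink occurs. In a Cox model, unlike a linear model, leaving out a strong predictor tends to move the treatment hazard ratio towards 1 even when randomisation balances that predictor, and power can fall with it.

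The article treats its primary outcomes unevenly. PDA and HDD are analysed with their T1 values, while TFD has no stated baseline term although the data come from the same interviews. What is at stake is efficiency on one of three primary outcomes. Type I error is not at stake.

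**Working it through.** **1. The plan's own figure.** Inputs (Power calculation): α = 0.05, power 0.80, w = 0.25, df = 3. The noncentrality needed for a 3-df chi-square test is λ = 10.90, so N = λ/w² = 10.90/0.0625 = 174.4. The stated 174 is reproduced, with power 79.9%. At N = 246, λ = 246 × 0.0625 = 15.4 and power is 92.4%. No input is a hazard ratio, an event rate or a goal share, so this figure says nothing about omitted predictors. The effect of omission has to be simulated under assumptions.

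**2. Goal-stratified versus unadjusted model.** Assumed: 82 per arm, exponential first-drink times censored at day 90, 40% first-drink probability in abstinence-goal controls, hazard ratio (HR) 0.55 in both active arms and for both goal groups, 2-df likelihood-ratio test.

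| Non-abstinence share, goal HR | Power unadjusted | Power stratified |
|---|---|---|
| 20%, 2 | 0.65 | 0.65 |
| 20%, 3 | 0.64 | 0.67 |
| 35%, 3 | 0.69 | 0.75 |
| 35%, 5 | 0.62 | 0.82 |

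Other runs of the last row gave 0.61/0.80 and 0.59/0.79. The unadjusted HR averaged between 0.55 and 0.62. Type I error was 0.045 and 0.051 for the two models. The last row implies many events: 0.65 × 0.40 + 0.35 × (1 − 0.60⁵) = 0.26 + 0.32 = 58% of controls.

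**3. Varying the event rate.** Assumed: 246 patients 1:1:1, HR 0.60 in both active arms, goal as a covariate, 2-df Wald test, 1,500 runs per cell. Entries are power without goal → with goal.

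| Share, goal HR | 10% control events | 33% | 60% |
|---|---|---|---|
| 20%, 1.5 | 0.081 → 0.081 | 0.397 → 0.393 | 0.665 → 0.668 |
| 20%, 2 | 0.075 → 0.082 | 0.356 → 0.362 | 0.655 → 0.688 |
| 40%, 2 | 0.087 → 0.086 | 0.374 → 0.395 | 0.639 → 0.689 |
| 40%, 3 | 0.090 → 0.097 | 0.360 → 0.413 | 0.593 → 0.691 |
| 30%, 5 | 0.083 → 0.090 | 0.341 → 0.412 | 0.489 → 0.717 |
| HR without goal | 0.606–0.612 | 0.598–0.632 | 0.604–0.669 |
| HR with goal | 0.600–0.610 | 0.594–0.601 | 0.598–0.603 |

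The Monte Carlo standard error of a single power near 0.65 is √(0.65 × 0.35/1500) = 0.012, so differences of a point or so are noise.

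**4. Which event rate?** The only figure in the article is that one third relapse within a year (Background). Under a constant hazard that is 1 − (2/3)^(1/4) = 9.6% at 3 months. Relapse need not mean any first drink, and early relapse would raise the share.

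A rate near 10% also fits poorly with w = 0.25. Read w as a difference in 90-day event proportions with equal active arms (an assumption), so that w² = (2/9)(p₀ − p₁)²/[p̄(1 − p̄)]. With p₀ = 0.10 this needs p₁ ≈ 0.0025: (2/9) × 0.0975²/(0.035 × 0.965) = 0.0625, an HR of about ln(0.9975)/ln(0.90) = 0.02. The same reading gives an HR of about 0.32 at 33% control events and 0.45 at 60%.

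**5. If training works only in abstinence-goal patients.** With the four scenarios of step 2 but no effect in the non-abstinence group, unadjusted versus stratified power is 0.37/0.34, 0.36/0.34, 0.25/0.21 and 0.21/0.18. Stratifying then loses 2 to 4 points.

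**The case against.** The strongest reply is that the article is silent rather than wrong. A reader might infer that it fixes a model containing the intervention and nothing else. It does not: the wording excludes nothing, the Trail Making Test is named as a covariate in another section, and covariate lists are commonly left to a full protocol or SAP, which is not shown. This stands, and it rules out calling the model an error. It does not remove the case for naming baseline drinking and goal, because the Trail Making Test supplies neither.

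A second reply is that the motivation undercuts the remedy. If a planned first drink is no failure of inhibition, training may do little for those patients, and step 5 shows that stratifying is then slightly worse. This stands as a real, small cost.

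Third, PDA and HDD already describe drinking in patients who do not aim at abstinence, so the trial does not rest on TFD alone. This also stands and limits what is at stake.

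Finally, a reader might infer that chance imbalance in goal biases the comparison. It does not. Under randomisation such imbalance is covered by the error rate of the test, and the unadjusted hazard ratio is a marginal one, not a wrong one.

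**Conclusion.** The point holds as an optional efficiency improvement. The stated TFD model has no baseline drinking or goal term although both variables are collected, and such terms can recover power in a Cox model.

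One might read this as showing that the training effect is diluted and power is lost. The documents do not support that: they give no goal distribution, goal hazard, training hazard ratio or 3-month event rate. Under the assumed ranges the loss from omitting goal runs from about 0 to just over 20 points. It is about 1 point or less at 10% control events and at most about 5 points with a goal hazard ratio of 2 or less. It reaches 10 points or more only when control events approach 60% and the goal hazard ratio is 3 to 5. The gain from T1 drinking was not simulated; it follows from the same mechanism, but its size is unknown. The sample size of 174 for TFD and the total of 246 are unaffected.

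**What to change.** Before unblinding, state for the TFD Cox regression:

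- T1 PDA from the TLFB interview is a covariate.
- Drinking goal (total abstinence versus any other) is a covariate or stratum, provided the sponsor confirms that it was recorded before the first training session. A goal recorded later may already reflect the training and should not be used.
- The unadjusted model is reported as a sensitivity analysis, and training group × goal as exploratory.

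The cost is one or two sentences and no new data, if a pre-training goal exists. The hazard ratio becomes conditional on the baseline terms and should be labelled so. About 2 to 4 points of power are lost if training has no effect in patients with a non-abstinence goal. Fixing this before results are known matters, because adding goal afterwards would look data-driven.

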There are two putative working mechanisms by which alcohol-specific inhibition training is thought to be effective. The first is through enhancing inhibitory capacities in the context of alcohol-related cues, which can be assessed with inhibitory tasks, such as the Go-NoGo Task (GNG) or the Stop-Signal Task (SST). The second putative working mechanism regards devaluation of the stimuli. It is based on the *Behavior Stimulus Interaction Theory* [38], which states that the repeated stopping response to the rewarding (alcohol, in this context) stimuli causes a devaluation thereof [31, 33]. This mechanism is thus thought to alter the automatically attributed appeal of alcohol-related stimuli, an effect which can be measured with the Implicit Association Test (IAT).

With respect to the devaluation mechanism, the first two studies were consistent with predictions of the *Behavior Stimulus Interaction Theory* in their reports that participants’ implicit attitudes shifted towards a more negative evaluation of alcohol-related stimuli after alcohol-specific inhibition training [32, 33]. However, this finding could not be replicated in the four subsequent studies [34–37].

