#### Go-NoGo Task (GNG)

This task measures response inhibition in both an alcohol-specific and a neutral context. In the modified version of Stein et al. [25], eight pictures of alcoholic beverages (beer, wine, or spirits, according to the participants drink of choice) and eight neutral beverages (water) are presented on screen at a presentation rate of 1 Hz. The pictures are displayed on-screen for 900 ms and the inter-stimulus interval is 100 ms. Participants are instructed to click a button as soon as a stimulus appears on screen (Go trial) unless the same stimulus appears twice in a row (NoGo trial). Each of the 16 pictures will be presented 60 times during the task: 52 times as a Go trial and eight times as a NoGo trial, resulting in a Go/NoGo ratio of 6.5. This ratio is intended to establish a high tendency to respond, making action restraint difficult. In total, the whole experiment thus includes 960 trials (416 neutral Go trials, 416 alcohol-related Go trials, 64 neutral NoGo trials, and 64 alcohol-related NoGo trials), which are presented in a pseudorandomized order, controlling for position, sequential order, and requiring a minimum of two Go trials between two NoGo trials. Half way through, participants are allowed a pause of a self-determined length. The whole task takes approximately 18 min to complete.

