#### Stop-Signal Task (SST)

As a second measure of response inhibition, a Stop-Signal Task (SST) will be performed, which includes four pictures of alcoholic beverages located inside a building and four neutral pictures of objects located outside. After a fixation cross, which lasts 460 ms, the individual pictures will appear on a computer screen and participants will be instructed to press the button “a” (left) or “l” (right) as soon as possible to indicate whether the picture was taken inside (confounded with alcohol-related content) or outside a building (confounded with neutral content). During instructions, this pairing of location (inside, outside) and content (alcohol, neutral) is not mentioned. An exception to the rule is to be made when an auditory stop signal occurs (NoGo; 25% of the trials). This stop signal starts with a delay of 100, 200, or 300 ms (each comprising one third of NoGo trials) after stimulus onset. As this stop signal appears after the picture, and not simultaneously with it, as during the GNG or the training, task performance in the SST depends on action cancellation and thus measures a slightly different aspect of response inhibition. After completion of two practice blocks each, two test blocks comprising 240 trials each (180 Go and 60 NoGo trials) will be completed. The key allocation is counterbalanced, and the order of trials is pseudorandomized. As an indicator of response inhibition, the stop-signal reaction time (SSRT) will be computed for alcohol-related and non-alcoholic pictures according to the algorithm described in Houben, Havermans [32].

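### The planned ANOVA for the inhibition tasks has no term that tests whether a gain is specific to alcohol pictures

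*Protocol article*

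**What the plan says.** The Main study paragraph under Statistics gives the model for the experimental test parameters as a "2 × 2 × 3 repeated measures ANOVA with the factors measurement point (T2, T3), time of day (morning, afternoon) and training group". The Power calculation section sizes the same layout, a "repeated measures ANOVA examining training effects on experimental parameters and also taking into account the effects of time of day of the training". Neither place names stimulus type, and no alcohol-minus-neutral score is defined for the Go-NoGo Task (GNG) or the Stop-Signal Task (SST).

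Both tasks are built to give the two conditions within each patient:

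- GNG: "This task measures response inhibition in both an alcohol-specific and a neutral context", with 64 NoGo trials of each kind.
- SST: "the stop-signal reaction time (SSRT) will be computed for alcohol-related and non-alcoholic pictures".

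The Background gives the first of two putative mechanisms as "enhancing inhibitory capacities in the context of alcohol-related cues", and it treats the difference between substance-related and neutral inhibition as clinically relevant. Stimulus type does appear in the EEG substudy analysis of the same tasks.

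**The concern.** The trial collects the contrast that would separate an alcohol-specific gain from a general one, then states a behavioural model without it. The model can be applied in two ways:

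- **Pooled over pictures.** An alcohol-only gain and a smaller gain on all pictures look the same.
- **Separately by picture type.** The alcohol analysis also rejects when the gain is fully general. Specificity would then have to be read from one significant and one non-significant p-value, which is not a test of the difference.

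The Discussion concedes that the control training may itself raise general inhibition. The 75/25 arm also differs from control in its Go/NoGo ratio, so a general change in that arm is a real alternative explanation. What is at stake is the mechanism claim, not the primary efficacy result.

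**Working it through.** **Inputs from the Power calculation section.** Alpha 0.05, power 0.80; "expecting small to medium effects of f = 0.15 and correlations of 0.4 among repeated measures based on earlier studies"; 82 per training group, N = 246. *Assumed, because the document does not give them:* c, the correlation between a patient's alcohol and neutral change scores (0.3 to 0.8), and q, the share of the effect that carries over to neutral pictures (0 or 0.5).

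**Step 1: reproduce the plan's figure.** The article states that "the necessary sample size was *n* = 180". For the within-between interaction with six cells and m = 2 measurements, λ = f²·N·m/(1−ρ), df = 5 and N−6.

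- N = 177: λ = 0.0225 × 177 × 2/0.6 = 13.275, power 0.801. This is the smallest N that reaches 0.80.
- Six equal cells round it up to 180: λ = 13.5, power 0.809.

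The stated figure reproduces with T2 and T3 as the only repeated measures, so the model that was powered had no stimulus factor. No sample-size figure is wrong.

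**Step 2: the three-group test at N = 246.** Take the SD of a single measurement as 1. The variance of a T3−T2 change is 2(1−0.4) = 1.2. The SD of the group mean changes is 2f = 0.30. If both Alc-IT arms gain d and control gains 0, that SD equals d√2/3, so d = 0.636.

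- Alcohol pictures alone: λ = 246 × 0.30²/1.2 = 18.45, df 2, power 0.98.
- Mean over both picture types (effect halved, variance 1.2(1+c)/2): λ = 18.45/[2(1+c)].
- Group × time × stimulus (variance 2 × 1.2(1−c)): λ = 18.45(1−q)²/[2(1−c)].

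| c | Pooled, q = 0 | Interaction, q = 0 | Interaction, q = 0.5 |
|---|---|---|---|
| 0.3 | λ 7.10, 66% | λ 13.18, 91% | λ 3.29, 35% |
| 0.5 | λ 6.15, 59% | λ 18.45, 98% | λ 4.61, 47% |
| 0.8 | λ 5.13, 51% | λ 46.1, >99% | λ 11.5, about 87% |

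At c = 0 the pooled and interaction tests have equal power, 78% (λ = 9.225 for both).

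**Step 3: can the planned test tell the explanations apart?** Simulated rejection rates with 4,000 trials, 82 per arm and c = 0.5:

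| True gain in the Alc-IT arms | Pooled | Alcohol only | Neutral only | Interaction |
|---|---|---|---|---|
| d on alcohol pictures only | 0.59 | 0.98 | 0.05 | 0.98 |
| d/2 on both | 0.59 | 0.47 | 0.47 | 0.05 |
| d on both | >0.99 | 0.97 | 0.98 | 0.05 |

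The pooled test gives the same rate in the first two rows. The alcohol-only test rejects equally often in the first and third. Only the interaction separates a specific gain from a general one.

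**Step 4: a limit of the interaction in the GNG.** The GNG's neutral pictures are water, from the set also used in training. In Table 1, water is always Go in both Alc-IT arms (80 Go, 0 NoGo) and evenly split in control (40/40). The interaction depends only on the alcohol-minus-neutral difference. A loss of size d on water with no gain on alcohol therefore gives the same λ as a gain of size d on alcohol, and so the same 91% to over 99% rejection.

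**The case against.** The case for leaving the model alone is substantial, and several parts of it stand.

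- **The research question is answered.** The Research questions section asks whether Alc-IT enhances response inhibition compared with control training. That is group × time. No listed question asks for a larger gain on alcohol than on neutral pictures, and a gain on both would contradict no stated hypothesis. A reader might infer that the planned ANOVA fails its own research question; the text does not support that.
- **Practice is already controlled.** A reader might infer that without the stimulus contrast a practice effect could pass for the mechanism. Table 1 rules this out for the 50/50 arm: it and the control training both have 160 Go and 160 NoGo trials and the same numbers of each picture type, and differ only in the pairing. The 75/25 arm (240 Go, 80 NoGo) is not matched in this way.
- **Power need not be lost.** Pooling is one reading of the text. If the alcohol parameter is analysed, power is 98%. A reader might take f = 0.2 and arrive at pooled power of only 30% to 39%, but that f is stated for PDA and HDD, not for these tasks.
- **Comparing two p-values would seldom mislead at this effect size.** With equal gains of size d on both picture types, the pattern of alcohol significant and neutral not arises in only about 2% of trials. It would be commoner with smaller effects.
- **A score could be defined elsewhere.** An alcohol-minus-neutral score would fit the 2 × 2 × 3 layout, and an analysis plan that is not shown may define one. However, the article does not leave the model open. It lists the factors and powers that same model, with no stimulus term in either place.

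What remains is narrower: nothing in the stated analysis tests alcohol specificity.

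**Conclusion.** The point holds in a limited form. The planned model tests whether Alc-IT improves inhibition more than control training. It does not test whether the improvement is specific to alcohol pictures, so a claim of alcohol-specific inhibition would have no stated test behind it.

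For an alcohol-only effect at the protocol's own f and ρ, the test that is missing would have 91% to over 99% power for c between 0.3 and 0.8. Pooling would have 66% to 51%. These figures rest on the assumed c, on full retention of 246 patients, on both Alc-IT arms gaining equally, and on f = 0.15, which here means a differential gain of 0.64 SD. Smaller effects, or carry-over to neutral pictures, reduce the power of the interaction, to about 35% to 87% at half carry-over. A non-significant interaction would therefore not show that the gain is general.

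PDA, HDD and TFD are not touched. Nor is the IAT, whose score is already a contrast.

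**What to change.** For GNG commission errors and for SSRT:

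1. Add stimulus type (alcohol, neutral) as a within-patient factor, or analyse an alcohol-minus-neutral score in the existing layout.
2. Keep training group × measurement point on the alcohol parameter as the test of enhanced inhibition.
3. Name training group × measurement point × stimulus type as the test of alcohol specificity, and state its power over a range of assumed correlations.
4. Always report the alcohol and neutral simple effects. Claim alcohol-specific improvement only if the alcohol simple effect shows a gain, because in the GNG the interaction alone could reflect worse inhibition to water. The SST uses untrained everyday objects as its neutral pictures and does not share this problem.

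The change needs no new patients or measurements. The article reports data collection as ongoing and defers the main analyses of the training effect until it is complete, so the change can be fixed beforehand. The cost is lower power for the interaction than for the alcohol-only test when the correlation is low (91% against 98% at c = 0.3; 78% at c = 0) or when the effect carries over, which is why item 2 stays.
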